### Recruitment of general practitioners (GPs)

In London, the criteria for inclusion of general practitioners (GPs) were a known interest in primary care for older people, routine use of computerised practice information systems, and practice location in suburban London. Overall, 4 group practices with a total of 26 GPs were recruited (Figure 2). The independent study centre randomly allocated three group practices (18 GPs) to training in risk identification and preventative geriatrics, and one group practice (8 GPs) to the concurrent comparison group.

In Hamburg, GPs registered in the entire metropolitan area were invited to participate via the newsletter of their regional GP association (BDA-Landesverband Hamburg). Overall, 21 GPs (organised in solo practices) agreed to participate (Figure 3) and the Hamburg study centre formed seven groups of three GPs matched for physician age, gender, and qualification (family practice versus internal medicine). In each group of three practitioners, the Hamburg study centre allocated two GPs to training and one GP to the concurrent comparison cohort.

In Solothurn, the cantonal authority selected three mainly rural primary care service areas. The Solothurn study centre obtained agreement to participate from all 33 GPs practising in these pre-selected areas (Figure 4). In each project area, these GPs (mostly organised in single-handed or small group practices) collaborated in practice circles consisting of 8 to 14 GPs each. Each practice circle had monthly meetings to organise emergency care in the region, to exchange practice policy information, and for continuing education. The independent study centre randomly allocated two practice circles to training and those from the remaining circle to the concurrent comparison group.

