### Sample size/power calculation

We calculated the required sample size for detecting, at a two-sided significance level of 0.05 and with a power of 80%, a postulated 30% difference in positive health risk behaviour or preventative care use in the intervention group as compared to controls at the one-year follow-up. For this calculation, a prevalence of positive behaviour or preventative care use among controls of 20% was assumed, based on pilot data in a comparable sample of community-dwelling older persons [6]. Based on a 1:1 randomisation ratio and a predicted drop-out rate at one year of 20%, the required sample size was 1000 persons per group. In Hamburg and Solothurn, due to limitations in resources available for offering the intervention (group sessions, home visits), a randomisation rate of 1:2 was preferable. Based on a 1:2 randomisation rate, and on the same drop out rate, the required sample size was 763 persons in the intervention group and 1525 persons in the control group.

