We will also evaluate changes in preventative care use, health behaviour, and health status between baseline and the one-year follow-up among persons in the intervention group. This analysis will be possible because persons in the intervention group received the HRA-O questionnaire both at base-line and at one-year follow-up. This analysis will adjust for household membership and base-line variables (age, gender, self-perceived health status, health care use prior to base-line). These pre-post analyses will be restricted to the intervention group since primary outcomes were not measured in the control group at baseline.

Outcome analysis of data from the concurrent comparison group will include a comparison of primary and secondary outcomes between the intervention group and the concurrent comparison group. The primary analysis will be a comparison of primary outcomes adjusted for base-line factors.

Categorical and binary outcome data will be analysed using chi-square tests; continuous outcome data will be compared using t-tests if normally distributed, Mann-Whitney U test if skewed. Number of physician visits will be analysed with ordered logistic regression models. To allow for within-household clustering, Generalised Estimating Equations (GEE), assuming an exchangeable correlation structure, will be used to analyse all outcomes [27]. Data will be analysed using the SAS programme [29].

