An additional limitation of the PRO-AGE study is the fact that the study was not powered to measure the effects of the intervention on the prevention of functional decline and nursing home admissions. However, it is appropriate, as a first step, to conduct a study for identifying effective intervention methods in the short-term, and in a second step, to plan new studies to evaluate the effects of an optimised intervention strategy over longer time periods.

A further limitation of this study is the possibility of contamination effects. Patients allocated to control groups may have benefited from the intervention because they received usual care from their GPs who had received special training and were involved in the intervention (Table 1). In anticipation of this problem, the study design includes outcome evaluations in a parallel concurrent comparison group with patients receiving care from physicians who had not received training in preventative geriatric medicine. A comparison between intervention and concurrent comparison group is expected to give an estimate of treatment effects without contamination bias, but is limited due to potential selection bias. In fact, there were some small but significant differences in base-line characteristics between participants of the intervention and concurrent comparison groups. Among other factors, this might be related to the fact that the number of clusters randomised was only 4 in London, and 3 in Solothurn. To address this limitation, the analyses comparing outcomes between intervention and concurrent comparison groups will adjust for base-line characteristics.

In conclusion, recruitment of study participants to this project was successful, and base-line findings confirm the success of the randomisation and the comparability of base-line characteristics between intervention and control groups. The a priori analytic plan which examines intervention effects takes into account the described limitations, and includes sensitivity analyses evaluating potential sources of bias. Furthermore, the database containing cross-sectional and longitudinal information on multiple health risks in older people will also be useful for refining existing instruments or methods of risk prediction in older people.

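### The intervention versus concurrent-comparison analysis models household clustering only, although group membership was set by practice, GP or practice circle, so its intervals and p-values omit between-provider variance

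*Protocol article*

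**What the plan says.** The section on recruitment of general practitioners describes how the comparison group was formed.

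- **London:** practices were assigned at random, as follows: "three group practices (18 GPs) to training in risk identification and preventative geriatrics, and one group practice (8 GPs) to the concurrent comparison group".
- **Hamburg:** 21 solo GPs were put into seven matched groups of three. In each, two went to training and one to the comparison cohort. The text does not say that this step was random.
- **Solothurn:** of three practice circles, two were randomly allocated to training and one to comparison.

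Statistical analyses gives the planned contrast with the intervention group: "The primary analysis will be a comparison of primary outcomes adjusted for base-line factors". The same section fixes the clustering level: "To allow for within-household clustering, Generalised Estimating Equations (GEE), assuming an exchangeable correlation structure, will be used to analyse all outcomes".

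The Discussion presents this contrast as the design's answer to contamination of the control group. It "is expected to give an estimate of treatment effects without contamination bias", with potential selection bias acknowledged. The Discussion also notes that only 4 clusters in London and 3 in Solothurn were randomised, offers this as a possible reason for baseline differences, and answers it with baseline adjustment.

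**The concern.** Patients of the same practice, GP or circle can resemble each other in the outcomes. This is most plausible for provider-driven items in Table 2, such as vaccination, cholesterol and glucose measurement and faecal occult blood testing. When whole providers are assigned to one side, that resemblance adds to the variance of the group difference. A GEE clustered on household cannot see it: households are small, while the allocated units hold from about 63 to 1171 patients. Adjusting for patient covariates can reduce imbalance, but it does not supply the missing variance term.

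This is more than something a condensed article leaves out. The text names the clustering level for all outcomes, recognises that the clusters are few, and names covariate adjustment as the remedy. If the randomised comparison shows little, readers will turn to this contrast as the one free of contamination. An ordinary difference between practices could then be reported as a significant intervention effect.

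**Working it through.** **1. The article's own sample size.** Inputs from the sample size section: a two-sided 5% level and 80% power. The target effect is "a postulated 30% difference in positive health risk behaviour or preventative care use in the intervention group as compared to controls". On the control rate, "a prevalence of positive behaviour or preventative care use among controls of 20% was assumed". For attrition and size at 1:1, the section gives "a predicted drop-out rate at one year of 20%, the required sample size was 1000 persons per group". Reading the 30% as relative gives 20% vs 26%.

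- Uncorrected n = [1.96·√(2·0.23·0.77) + 0.8416·√(0.20·0.80 + 0.26·0.74)]² / 0.06² ≈ 772 per group.
- With continuity correction: 805. Divided by 0.80: 1007 (stated 1000).
- At 1:2 with continuity correction: 596 intervention, giving 745 and 1490 after drop-out (stated 763 and 1525).

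The stated figures reproduce within 3% with an independent-patient formula. They concern the randomised comparison. The article gives no sample size, ICC or design effect for the concurrent-comparison contrast.

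**2. Variance inflation.** Enrolled numbers come from Table 4 and cluster counts from the GP recruitment section. With m patients per allocated cluster:

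- design effect per arm: DE = 1 + (m − 1)·ICC
- variance ratio: VIF = (DE_I/n_I + DE_C/n_C) / (1/n_I + 1/n_C)
- SE ratio = √VIF
- true error of a nominal 5% test = 2·[1 − Φ(1.96/√VIF)]

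The ICC is an assumption throughout.

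| Site and level | Patients/clusters, intervention | Patients/clusters, comparison | SE ratio, ICC 0.005 | SE ratio, ICC 0.05 | True error over that range |
|---|---|---|---|---|---|
| London, practice | 1240/3 | 636/1 | 1.9 | 5.4 | 31% to 72% |
| Hamburg, GP | 878/14 | 746/7 | 1.2 | 2.3 | 10% to 39% |
| Solothurn, circle | 874/2 | 1171/1 | 2.2 | 6.2 | 37% to 75% |
| Solothurn, GP only | 874/22 | 1171/11 | 1.2 | 2.1 | 9% to 35% |

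Example, London at ICC 0.005: DE_I = 1 + 412.3·0.005 = 3.06; DE_C = 1 + 635·0.005 = 4.18; VIF = 3.80; √3.80 = 1.95.

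The last row assumes that the 33 Solothurn GPs split 22 and 11, because the text gives only a range of 8 to 14 per circle. A comparison circle of 8 or of 14 GPs moves that row to 1.2–2.3 or 1.1–2.0.

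**3. Sensitivity.**

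- *Responders.* In London, Table 4 has at most 478 of 636 comparison patients with one-year questionnaire data. With 478, and 20% drop-out in the intervention arm (992), the London ratio is 1.8 to 4.7. The same approach for Solothurn at circle level (845 and 699) gives 2.0 to 5.4.
- *Very low ICC.* At 0.001 the true error is about 12% in London, 14% in Solothurn at circle level and 6% in Hamburg.
- *Household term.* The ratios take independent patients as the base. If household correlation already multiplies the variance by 1.25 (assumed: 1.5 participants per household, correlation 0.5), London becomes √[(1.25 + 2.80)/1.25] = 1.8 to √[(1.25 + 27.98)/1.25] = 4.8.

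**4. What needs no ICC.** London has four clusters and Solothurn three, with one comparison cluster each. The smallest attainable one-sided randomisation p-value is 1/4 in London and 1/3 in Solothurn. A cluster-level t-test would have 2 and 1 degrees of freedom (critical values 4.30 and 12.71).

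**5. Townsend score, London (Table 4).** Intervention 1.1 ± 3.0 (1197); comparison 4.4 ± 1.6 (635). Standardised difference = 3.3/√[(3.0² + 1.6²)/2] = 1.37; t = 3.3/√(3.0²/1197 + 1.6²/635) ≈ 31. The footnote says that differences at P < 0.05 carry an asterisk, and this one has none. The text calls the baseline differences minor and, in the Discussion, small.

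**The case against.** Much of the case on the other side stands and limits the point.

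- **Household GEE.** Patients are not treated as wholly independent; household correlation is modelled for all outcomes. What is missing is the provider level.
- **ICC.** It is assumed, and one range need not suit every outcome. Six of the primary outcomes are personal behaviours, such as seat-belt use, diet and tobacco.
- **Solothurn.** A circle is a group of mostly single-handed or small practices that meet monthly. A correlation typical of one GP's patients need not extend across a circle, so the upper figure is a possibility and not a result.
- **Hamburg.** At ICC 0.001 the error rate is near nominal, so intervals that are grossly too narrow cannot be asserted there.
- **Disclosure.** The Discussion admits selection bias and few clusters. It does not admit understated variance.

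Three stronger inferences are tempting and not supported. A reader might say that the contrast is misdescribed because it mixes GP training with the health risk appraisal. Table 1, however, lists training of health professionals as a component of the intervention, so the contrast is the full intervention versus usual care. A reader might say that Townsend will be left out of the adjustment. It was collected as baseline data, the article promises adjustment for baseline factors, and nothing shows that it is excluded. As an area score, its gap is also no evidence about outcome ICCs. Finally, a reader might extend the criticism to the main trial result. There, households were randomised among the patients of trained GPs, and this point does not reach it.

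**Conclusion.** The point holds for the concurrent-comparison contrast. Carried out as written, the plan gives standard errors that omit between-provider variance, and the stated remedy does not address that. The size is conditional on the assumed ICC: substantial in London from about 0.005 upward, mild to moderate in Hamburg, and in Solothurn dependent on whether outcomes correlate within GPs only or across a whole circle. The structural part is firm without any ICC. With one comparison practice and one comparison circle, a significant p-value in London or Solothurn can arise only by assuming away between-cluster variance. The Townsend presentation is a secondary correction. This should be fixed, but it does not threaten the trial's main analysis, because the contrast is supplementary to the household-randomised comparison.

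**What to change.** - **Hamburg:** analyse at GP level within the seven matched triplets. For each triplet, take the mean of the trained GPs' intervention patients minus that of the comparison GP's patients, and use a t-test on 6 df. Alternatively, use GP as the GEE cluster with a small-sample correction.
- **London and Solothurn:** report adjusted differences as observational, with intervals shown over a stated ICC range and no confirmatory p-values. State that the group effect cannot be separated from the single comparison practice or circle. Making practice or circle the GEE cluster would not help, since robust standard errors are unreliable with three or four clusters.
- **Text:** name Townsend among the London adjustment covariates, add the missing asterisk in Table 4, and correct the description of the baseline differences as minor or small.
- **Not recommended:** adding a control versus concurrent-comparison contrast to gauge spill-over. It has the same one-cluster problem in London and Solothurn.

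The cost is wording and analysis code; no new data are needed. Intervals widen, and significance claims for this contrast are dropped in London and Solothurn.

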### Recruitment and inclusion of study participants

Figures 2 to 4 depict the flow of study participants in London, Hamburg, and Solothurn. As shown, the percentage of participating older persons varied according to study site. Among patients of trained physicians, the numbers of older persons (% of eligible) agreeing to participate were 2503 (66.0%) in London, 2580 (53.6%) in Hamburg, and 2284 (67.5%) in Solothurn. In the concurrent comparison group, the number of persons (% of eligible) agreeing to participate was 636 (48.8%) in London, 746 (35.7%) in Hamburg, and 1171 (63.0%) in Solothurn.

Table 3 lists the results of the analyses comparing age and gender of persons agreeing to participate with eligible patients who declined. This analysis is based on multivariate logistic regression analyses. In London those who declined to participate were on average about one year older than participants. A similar comparison of the recruitment process of the Hamburg randomised study did not reveal statistically significant differences. The interpretability of the Hamburg data is limited because demographic information was not available for a proportion of non-participants due to state-mandated data protection issues. The comparison between participants and non-participants of the Solothurn randomised study revealed a gender difference, with men declining participation more often as compared to women. The comparison between participants and non-participants of the Solothurn concurrent comparison group revealed the same age difference as found in London, with non-responders being approximately one year older as compared to responders.

**Table 3 T3:** Comparison of participants and non-participants in the PRO-AGE study at the three study sites

	**London (U.K.)**			**Hamburg (Germany) ***			**Solothurn (Switzerland)**		
	**Participants**	**Non-participants**	**P-value**	**Participants**	**Non-participants**	**P-value**	**Participants**	**Non-participants**	**P-value**

**Randomised study**									

Age (years)	74.6 ± 6.3 (2503)	75.7 ± 7.3 (1292)	<.0001	71.8 ± 7.6 (2580)	71.3 ± 8.1 (1234)	0.10	74.5 ± 6.0 (2284)	74.8 ± 6.8 (1098)	0.68
Female gender	54.9% (1375/2503)	58.3% (753/1292)	0.12	62.7% (1617/2580)	62.1% (821/1322)	0.70	56.6% (1293/2284)	52.7% (579/1098)	0.03

**Concurrent comparison group**									

Age (years)	74.9 ± 6.5 (636)	75.9 ± 7.5 (667)	0.01	72.0 ± 8.2 (746)	71.3 ± 8.5 (631)	0.31	74.2 ± 6.0 (1171)	75.1 ± 6.8 (687)	0.01
Female gender	57.6% (366/636)	57.4% (383/667)	0.63	68.1% (508/746)	63.7% (690/1084)	0.001	57.0% (667/1171)	60.0% (412/687)	0.32

PRO-AGE: PRevention in Older people – Assessment in GEneralists' practices

Values are percentages (nominator/denominator) or means ± standard deviations (denominator).

P-values based on multivariable logistic regression models including age and gender.

* In Hamburg, information on age and gender was in part missing amongst non-participants due to state-mandated data protection regulations.

### Comparison between groups of participants

Table 4 describes the available base-line characteristics of the study participants according to study sites and group allocation. This is to evaluate the success of randomisation. Within each site, prevalence rates were similar between intervention and control groups. In contrast, there were some relatively minor, but statistically significant differences between persons of the concurrent comparison group and persons of the intervention group (Table 4). Information on education, living alone status, and chronic conditions was derived from baseline HRA-O questionnaire (intervention groups: administered at the start of the project after randomisation; control and concurrent comparison groups: administered at the one-year follow-up). Missing values are due to non-response (all groups) or attrition (death, move away, and move to nursing home) in the control and concurrent comparison groups.

**Table 4 T4:** Self-reported baseline characteristics of the PRO-AGE study participants, according to site and group assignment

**Baseline characteristics**	**London (U.K.)**			**Hamburg (Germany)**			**Solothurn (Switzerland)**		
	**Intervention group**	**Control group**	**Concurrent comparison group**	**Intervention group**	**Control group**	**Concurrent comparison group**	**Intervention group**	**Control group**	**Concurrent comparison group**

Age (years)	74.7 ± 6.4 (1240)	74.4 ± 6.2 (1263)	74.9 ± 6.5 (636)	71.9 ± 7.7 (878)	71.8 ± 7.6 (1702)	72.0 ± 8.2 (746)	74.5 ± 5.8 (874)	74.5 ± 6.1 (1410)	74.2 ± 6.0 (1171)
Female gender	55.3% (686/1240)	54.6% (689/1263)	57.5% (366/636)	61.5% (540/878)	63.3% (1077/1702)	68.2%* (509/746)	56.9% (497/874)	56.5% (796/1410)	57.0% (667/1171)
Fair/poor self-perceived health	24.5% (304/1240)	27.2% (343/1263)	27.4% (174/636)	38.6% (339/878)	38.5 (656/1702)	39.5% (295/746)	19.9% (174/874)	24.8% (349/1410)	23.6% (276/1171)
≥1 hospital admission over past 12 months	14.0% (173/1240)	14.6%) (185/1263)	14.2% (90/636)	21.2% (186/878)	21.2% (360/1702)	22.5% (168/746)	19.9% (174/874)	18.5% (261/1410)	17.7% (207/1171)
> 6 doctor visits over past 12 months	19.0% (236/1240)	24.3% (307/1263)	23.4% (149/636)	49.9% (438/878)	49.9% (849/1702)	44.0%* (328/746)	24.0% (210/874)	24.3% (343/1410)	28.7%* (336/1171)
No available caregiver if needed	17.6% (218/1240)	14.8% (187/1263)	19.2% (122/636)	17.8% (156/878)	18.9% (322/1702)	20.0% (149/746)	9.8% (86/874)	11.6% (163/1410)	8.8% (103/1171)
Pra score	0.27 ± 0.11	0.27 ± 0.11	0.27 ± 0.11	0.30 ± 0.11	0.30 ± 0.12	0.29 ± 0.11	0.29 ± 0.104	0.29 ± 0.11	0.30 ± 0.11
Low level of education	59.8% (666/1113)	62.5% (654/1046)	71.9%* (343/477)	18.8% (142/756)	23.5% (300/1277)	25.0%* (135/539)	47.7% (335/702)	43.2% (398/921)	41.9%* (337/804)
Living alone	33.6% (375/1116)	30.9% (324/1047))	36.4% (174/478)	35.0% (279/798)	37.4% (504/1349)	36.9% (206/559)	31.4% (234/745)	30.6% (299/976)	27.1% (229/845)
Three or more self-reported chronic conditions	33.3% (365/1095)	31.2% (324/1039)	39.0%* (183/469)	52.3% (399/763)	53.3% (691/1296)	52.3% (287/549)	39.5% (285/722)	39.6% (364/920)	42.6% (344/808)
Townsend score	1.1 ± 3.0 (1197)	1.0 ± 3.0 (1247)	4.4 ± 1.6 (635)	n.a.	n.a.	n.a.	n.a.	n.a.	n.a.

PRO-AGE: PRevention in Older people – Assessment in GEneralists' practices

n.a. denotes not available.

Values are percentages (nominator/denominator) or means ± standard deviations (denominator).

Statistically significant differences (bivariate analyses, P < 0.05) between intervention and concurrent comparison group are marked with an asterisk.

Pra score (Probability of repeated admissions): higher scores denote higher risk for hospital admission.

Townsend score: higher scores denote higher social deprivation.

## Discussion

To our knowledge this is the first randomised study of a HRA-O intervention conducted in Europe. As shown in this paper, the PRO-AGE project was successful in recruiting the large number of older persons required to evaluate – with adequate statistical power – the effects of a HRA-O intervention on health behaviour and use of preventative care. The PRO-AGE project has additional strengths. The HRA-O intervention was implemented in three sites in different countries, with different health care systems, different languages and different cultural backgrounds. Furthermore, each site implemented an additional specific reinforcement of the HRA-O. Thus, this study can evaluate the effects of HRA-O with varying forms of reinforcement in a broad range of older persons. Finally, based on the planned risk-stratified analyses using the Pra questionnaire, it will be possible to evaluate whether effects are more positive in persons at low risk, as compared to persons at high risk, as suggested by recent research evidence [28].

The PRO-AGE project has several limitations. Firstly, one-year outcome analysis is based on self-reported information alone, and there is no systematic information from direct patient observation, no cost data, and only limited information from medical records available for this analysis. However, since we used validated instruments to obtain information on a broad range of health-related measures, the study will provide valid estimates on the effects of HRA-O on health behaviour, preventative care use, and health status in older persons.

Second, outcome data will not be available for a part of the study participants due to missing data. Due to budgetary constraints it was not feasible to implement a reminder system or use some other mechanism for obtaining outcome data from persons who did not respond or only partially responded to the one-year follow-up questionnaire. The magnitude of this limitation will depend on the percentage of missing information among study participants at the three study sites. The potential impact of missing data will be evaluated in statistical sensitivity analyses.

An additional limitation of the PRO-AGE study is the fact that the study was not powered to measure the effects of the intervention on the prevention of functional decline and nursing home admissions. However, it is appropriate, as a first step, to conduct a study for identifying effective intervention methods in the short-term, and in a second step, to plan new studies to evaluate the effects of an optimised intervention strategy over longer time periods.

A further limitation of this study is the possibility of contamination effects. Patients allocated to control groups may have benefited from the intervention because they received usual care from their GPs who had received special training and were involved in the intervention (Table 1). In anticipation of this problem, the study design includes outcome evaluations in a parallel concurrent comparison group with patients receiving care from physicians who had not received training in preventative geriatric medicine. A comparison between intervention and concurrent comparison group is expected to give an estimate of treatment effects without contamination bias, but is limited due to potential selection bias. In fact, there were some small but significant differences in base-line characteristics between participants of the intervention and concurrent comparison groups. Among other factors, this might be related to the fact that the number of clusters randomised was only 4 in London, and 3 in Solothurn. To address this limitation, the analyses comparing outcomes between intervention and concurrent comparison groups will adjust for base-line characteristics.

In conclusion, recruitment of study participants to this project was successful, and base-line findings confirm the success of the randomisation and the comparability of base-line characteristics between intervention and control groups. The a priori analytic plan which examines intervention effects takes into account the described limitations, and includes sensitivity analyses evaluating potential sources of bias. Furthermore, the database containing cross-sectional and longitudinal information on multiple health risks in older people will also be useful for refining existing instruments or methods of risk prediction in older people.

